## Abstract

**Background:**

Depression is a big health concern and a leading cause of disability worldwide that is inadequately addressed. Severe somatic illnesses are often associated with psychological distress that can reach the level of a depressive disorder requiring treatment. Depression as a comorbidity is linked with a poor quality of life and noncompliance to treatment in these patients, which may lead to increased use of health services. Information on the frequency and the disease course of depression in patients with severe somatic diseases and the need for inpatient treatment and subsequent treatment is still lacking.

**Methods:**

A cohort study including patients with a diagnosis of cardiovascular diseases (heart attack, stroke, peripheral artery disease) or systemic inflammatory disease (rheumatoid arthritis, inflammatory bowel disease) who are admitted to the University Hospital of Augsburg will be established. At recruitment during hospital stay/outpatient visit, data on mental health (e.g. depressive symptoms, stress, quality of life), clinical data, and lifestyle data will be gathered through self-administered questionnaires and chart review. Furthermore, blood samples will be collected and stored. After hospital discharge, study participants will be repeatedly contacted over time (at the beginning in shorter intervals, then about every 3 months) to provide further information about their mental well-being, life circumstances (e.g. incapacity to work), quality of life, and utilization of medical services. Altogether at least 500 patients should be included and followed up in this study. Descriptive statistics including prevalence and group differences will be calculated. Multivariable generalized linear mixed-effects models with random intercepts will be performed to examine determinants of depression and predict the occurrence and course of the disease.

**Discussion:**

The strengths of the DESIE study are the mainly digital assessments and its longitudinal character with frequent follow-up questionnaires. The study will substantially contribute to the current research about comorbid depression in somatic diseases.

**Trial registration:**

The study was prospectively registered in the German Clinical Trials Registry and WHO International Clinical Trials Registry Platform (registration number: DRKS00033245, date of registration: 14 December 2023) prior to the start of recruitment.

## Background

Depressive disorders are a major public health problem both nationally and internationally, because of its relatively high prevalence and its association with significant disability [1, 2]

It is well known that numerous somatic illnesses are associated with depression. In a large World Health Survey including more than 240,000 participants from 60 countries, an average between 9.3 and 23.0% of participants suffering from at least one chronic somatic disease had comorbid depressive symptoms [2].

Approximately half of the adult population lives with one or more chronic diseases [3]. Many of them must cope with a range of challenges, such as difficult symptoms or loss of independence; even daily self-management could become a hurdle. Due to those challenges, people with chronic disease are at significantly increased risk of depression, compared to the general population [4, 5]. In addition, the co-occurrence of psychological distress in chronic disease is associated with a range of adverse outcomes, such as poorer self-rated health [6] increased work absenteeism [7], and poorer disease self-management and prognosis, including lower adherence to treatments and lifestyle recommendations [8].

Thus, in the context of somatic diseases, depression is of particular importance. Especially severe somatic diseases that are accompanied by inflammatory processes seem to increase the risk of depression [9]. Besides biological mechanisms (e.g., inflammation) [10], also psychological mechanisms (e.g., fear of the consequences of the somatic illness) or associated circumstances (e.g., the need to attend repeated appointments and examinations due to the somatic disease) may significantly promote the manifestation of depression.

In the context of the widespread diseases stroke and myocardial infarction, depression usually occurs after the acute event. Currently, there are only few options to support these patient groups. For example, the point prevalence of major depression after myocardial infarction is reported to be 28.7% [11]. Prevalence rates of depression are influenced by the severity of the underlying somatic disease [12]. A large cohort study of 157,243 stroke patients found that 25.4% of patients developed depression within two years of study entry compared with only 7.8% in the reference population [12]. However, also, patients with other physical disorders, such as peripheral artery disease [13], cancer [14] and autoimmune diseases [15, 16] show substantially higher frequencies of depressive disorder than observed in the general population.

Often, depressive disorders are diagnosed too late and thus also worsen the prognosis of the somatic disease. Depression impairs quality of life and social participation, leads to immense direct and indirect costs (especially sick days and reduced earning capacity), and places a burden on sufferers and their families. In addition, a large-scale meta-analysis based on 48 studies and 55,898 people showed that comorbid depression in somatic illness significantly increases treatment costs (16 studies, 1.39 95%CI 1.24—1.55, *p* < 0.001) [17].

There is evidence that psychotherapy and psychosocial approaches successfully reduce distress associated with chronic illness [18], thereby promoting successful adjustment. However, these treatments appear to be effective only in people who meet the criteria for a depressive disorder, as opposed to unselected samples [18]. Importantly, many patients appear to have increased depressive or anxiety symptoms after the onset of a chronic illness that resolves on its own (e.g., [19, 20]). This fits with the concept of psychological adjustment as a return to equilibrium after a stressor, with people using their resources to achieve a "new normal" [21, 22]. In such cases, psychological treatment may not be clinically necessary and thus not cost-effective. However, it is not clear what proportion of people with chronic illnesses consistently experience increased distress and when in the course of the disease the need for psychological treatment arises. A clear understanding of the proportion and timing of patients' psychological adjustment is important for the appropriate implementation and the success of psychological intervention in our health care systems.

Epidemiological studies suggest that fewer than 20% of individuals with depression are adequately treated [23]. The resource of professionals for timely diagnosis and treatment is limited [24, 25] leading to a situation of undersupply. In addition, due to demographic change, an increase in somatic diseases and, as a consequence, an increase in depression is to be expected [26]. Therefore, a major challenge in the coming years is to improve the care of people with mental illnesses, especially depression.

Data from Germany regarding the diagnosis and care of depression in people with a severe somatic disease is still scarce [27, 28]. In addition, none of these prior studies prospectively investigated the risk of depression in patients with somatic diseases.

The prospective DESIE study will investigate the frequency and the disease course of depression in patients with severe somatic diseases, that is myocardial infarction, stroke, peripheral artery disease or systemic inflammatory diseases. The main aim of the project is to identify patients who are already showing signs of depression at an early stage. A special feature of the DESIE study is that, unlike existing cohorts, it will collect data digitally at baseline and during follow-up. Based on the available data (personal characteristics, lifestyle data, clinical data, biomarker data), determinants will be analyzed; an algorithm will be developed to predict the development of depression and its course in each somatic disease entity.

As secondary research questions the acceptance of digital medicine in this patient group, health care utilization of patients with severe somatic diseases with and without mental health problems, and additional psychological impairments will be investigated.

## Methods

The present study is part of the digiBRAVE (digitales Bayerisches (Früh-)Diagnostik-, Präventions- und Therapieprogramm Depression) project at the University Hospital of Augsburg and the Bezirkskrankenhaus Augsburg with the aim to promote health and reduce the burden of disease through targeted digital prevention, diagnosis, and treatment of concomitant depression in somatic disease. The project will involve collaboration between different disciplines, namely digital medicine, psychiatry and psychotherapy, neurology, ethics, general medicine and epidemiology. It is funded by the Bavarian State Ministry of Health and Care.

The DESIE study will include patients who are hospitalized or visiting a clinical outpatient department due to a serious somatic disease at the University Hospital Augsburg. The focus of the present study is on the inclusion of patients with stroke, myocardial infarction, peripheral artery disease, and systemic inflammatory diseases (chronic inflammatory bowel diseases and rheumatoid arthritis). However, patients with other severe diseases (e.g. cancer, long-covid) may be included if they wish. Participation in the study is voluntary, irrespective of management strategy and outcome. If a patient is willing to take part in the study, a written informed consent form has to be signed by him/her. The data collection will be performed in accordance with the Declaration of Helsinki. The data underlies professional discretion and data protection according to the General Data Protection Regulation (GDPR). Personal identifying data and scientific data are stored separately under pseudonyms. Information on data protection is included in the written patient information and the consent forms.

At the University Hospital Augsburg trained study nurses prospectively record all cases of heart attacks, strokes, peripheral artery diseases, and systemic inflammatory diseases and visit the patient to inform her/him about the study and to deliver the study documents. Patients will receive comprehensive and understandable information on the processes and consequences of participation in the study. It is planned to recruit at least 500 patients during the project.

The required sample size was calculated, expecting a prevalence of 20% of depressive symptoms in patients with somatic diseases and a given type I error of 0.05. Depending on a specific determinant of interest (e.g. childhood trauma, level of education, perceived stress) with a true probability of at least 15% for depressive symptoms, the sample size needs to be at least 380 to achieve a statistical power of at least 0.8. Considering the comprehensive questionnaires and frequent follow-up time points, a drop-out rate of 25% can be expected based on previous experience with longitudinal studies. Therefore, the recruitment of at least 500 patients should be sufficient to answer several research questions. The sample size calculations were performed with the software PS (Power and Sample Size Calculations, Version 3.0).

Based on the experience in previous comparable studies, it is expected that this project aim can be reached. The recruitment phase is planned stepwise (staggered start of recruitment for the different disease entities) and will continue until May 2025. Recruitment of patients began in January 2024.

Inclusion criteria.Inpatient admission or visit at the clinical outpatient department of the University Hospital AugsburgAge 18 years and olderCapable of giving informed consentSufficient fluency in German to understand the implications of participating in the studyAdmission diagnosis (suspected diagnosis) of:Vascular disease such as stroke, peripheral artery disease or myocardial infarction (core group)Systemic inflammatory disease (core group)Other serious somatic diseases (e.g., cancer, long-covid), if they wish to participate in the study

Exclusion criteria.Lack of capacity to give consent (e.g. dementia, language difficulties)Age < 18 yearsNo interest in participating in the study

Patients with a physician diagnosis of depression prior to the hospital stay/outpatient visit will not be excluded from the study.

### Data collection at baseline hospital stay or visit at clinical outpatient department

After patients have signed the informed consent form, study nurses will hand over a standardized questionnaire during their hospital stay or a visit at a clinical outpatient department (either in the form of an online questionnaire via tablet computer or in paper–pencil form). The questionnaire will cover via a self-rating demographic information, comorbidities, lifestyle data (including physical activity), disease history, the PHQ-9 (Questionnaire to assess depressiveness) [29], the WHO-5 (World Health Organization (WHO) index of well-being) [30],

WHOQOL-BREF (quality of life) [31], the EQ-5D (EuroQol-5D) questionnaire [32], the Childhood Trauma Questionnaire (CTQ) [33], the Perceived Stress Questionnaire (PSQ) [34], questions about the acceptance of digital medicine (ADM) [35], subjective experience of discrimination (SDE), and self-stigmatization (SSMI questionnaire) [36]. Routinely collected clinical data on comorbidities, risk factors, medications prescribed, diagnostic procedures, clinical characteristics, laboratory parameters, and invasive and non-invasive treatment regimens as well as complications during hospital stay will be assessed by chart review. The decision of focusing on self-administered questionnaires has been made to facilitate recruitment and to allow for remote assessments during the follow-up periods.

### Follow-up surveys

All study participants are followed up at specific time points after being discharged from the hospital (see Table 1). Follow-up surveys can also be conducted online (survey link is sent via e-mail) or in paper–pencil form. Some of the questionnaires from the baseline survey are also used in the follow-up surveys. In addition, questions are asked about days of incapacity to work (if still working), visits to the doctor, inpatient admissions and return to work/training/education. After initially close follow-up time periods, the plan calls for surveys to be conducted every three months up to one year. Participants receive a reminder to complete the questionnaire via e-mail or phone call after three to seven days depending on the number of the follow-up survey.

**Table 1 Tab1:** Data collection as part of the DESIE study

Time points of data collection	T_0_ (Baseline)	T_1_	T_2_	T_3_	T_4—6_
Days	During hospital stay	14	28	90	every 90
PHQ-9 (patient health questionnaire)	X	X	X	X	X
WHO-5 (WHO index of well-being)	X	X	X	X	X
EQ-5D questionnaire	X	X	X	X	X
WHOQOL-BREF (quality of life)	X	X	X	X	X
PSQ (Perceived Stress Questionnaire)	X	X	X	X	X
CTQ (Childhood Trauma Questionnaire)	X				
Sociodemographic data	X				
Disease history	X				
Data on lifestyle	X				
ADM (acceptance of digital medicine)	X			X	
SDE (subjective experience of discrimination)	X				
SSMI (Self-stigmatization)	X				
Days of incapacity to work*			X	X	X
Doctor visits			X	X	X
Hospitalizations			X	X	X
Return to work/training place*			X	X	X

^*^if still employed or in training

### Collection of blood

During the hospital stay about 30 mL blood will be collected from the patients of the core group, that is patients with stroke, heart attack, peripheral artery disease, or systemic inflammatory diseases. If possible, blood samples will be taken as part of the routine blood tests scheduled for patients during their inpatient stay or outpatient appointments. Laboratory staff at the Chair of Epidemiology will be in charge of processing and aliquoting of the samples, and the storage of the sample tubes at −80 °C in the freezers at the Chair of Epidemiology.

### Patients with depressive symptoms

Generally, study participants are offered a leaflet with information about depression and where to get help. If patients show noticeable depressive symptoms during their hospital stay and study participation, the study nurses inform the attending physician for a psychiatric consultation including suicidality risk assessment. In addition, a digital stepped care program with digital services that can be individually tailored to the severity and intensity of depressive symptoms is concurrently developed for these patient group as a part of the superordinate project digiBRAVE.

If baseline data from participants with stroke indicate relevant symptoms of depression (PHQ-9 ≥ 10 points) a more detailed evaluation will be performed by study personnel. These individuals are immediately offered the opportunity to participate in an intervention study with tele-psychological treatment (DISCOVER study) [37], which is not part of this cohort study. All patients who accept the invitation to the intervention study must sign separate informed consent forms.

### Statistical analysis

After data cleaning, quality assurance, and transformation of variables descriptive statistics and explorative data analysis will be carried out.

The prevalence of psychological impairments and baseline characteristics will be reported by calculating appropriate summary statistics. Depending on their distributions, continuous variables will be presented either as means and standard deviations or medians and interquartile ranges. Where the normality assumption is met, differences between independent groups will be preferably tested using two-sided parametric statistical tests (i.e. *t*-test, ANOVA). Otherwise, equivalent non-parametric tests will be used (i.e. Mann–Whitney-U test, Kruskal–Wallis test). Considering re-measurements in the longitudinal design, corresponding parametric and non-parametric tests will be performed (i.e. paired *t*-test, Wilcoxon signed-rank test, repeated measures ANOVA, and Friedman’s test). If there are notable differences in more than two groups or time points, additional appropriate post-hoc tests will be conducted. Pairwise comparisons of categorical variables will be assessed using Fisher's exact test, while differences in frequencies over time will be tested with the Cochran’s Q test. Assumptions of normality, sphericity, and equal variances will be ensured performing Shapiro–Wilk test, Mauchly’s test, and Levene’s test, respectively.

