## Discussion

The DESIE study is a prospective, observational cohort study in which patients with severe somatic diseases (heart attack, stroke, peripheral artery disease, systemic inflammatory disease or other diseases) are recruited and their characteristics and outcomes measured longitudinally. The focus will lay on the digital assessment of mental health outcomes with the aim of implementing a mainly digitalized follow-up. Based on the data obtained during the project, an algorithm will be developed to predict the development of depression as it progresses. In addition, the care of patients with depression in chronic somatic diseases is to be improved.

The strength of this study is a comprehensive mainly digital baseline assessment, the collection of blood samples and its longitudinal character with frequent, mainly digital, follow-up questionnaires. However, the follow-up assessments can also be a limitation if a lot of participants drop out of the study. To overcome this limitation patients are informed comprehensively about the frequency and timing of the follow-ups and are reminded via e-mail or phone contact to complete the questionnaire. Another limitation is that patients with e.g. severe stroke may be not able or refuse to complete the questionnaire during their hospital stay due to physical or mental impairments which can lead to a selection bias towards less severe cases. Due to the very intimate and subjective nature of the topics, we did not consider proxy interviews (e.g. by a relative) to be appropriate, but the study nurses offer assistance to impaired patients and provide a shorter version of the baseline questionnaire if necessary. Furthermore, the study is planned as a single-centre study which limits generalizability as participants from one university hospital may differ from patients of other regions. However, after the initial funding phase, the study design may be expanded to further university hospitals in the future.

Overall, the DESIE study will make substantial contributions to the current knowledge about comorbid depression in somatic diseases. Based on the study results of DESIE, in combination with the superordinate project digiBRAVE involving various disciplines, screening, prevention, and treatment of comorbid depression may be enhanced.

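### Change over time is to be tested with methods that use only patients with a value at every visit tested, so a test over T0-T6 would keep at most 375 of 500 at the expected 25% drop-out

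*Protocol article*

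**What the plan says.** The Statistical analysis section opens by stating that "descriptive statistics and explorative data analysis will be carried out". On repeated measurements it says "Considering re-measurements in the longitudinal design, corresponding parametric and non-parametric tests will be performed" and lists "paired *t*-test, Wilcoxon signed-rank test, repeated measures ANOVA, and Friedman’s test"; for categorical outcomes, "differences in frequencies over time will be tested with the Cochran’s Q test". Post-hoc tests follow where more than two groups or time points differ. It adds: "Assumptions of normality, sphericity, and equal variances will be ensured performing Shapiro–Wilk test, Mauchly’s test, and Levene’s test, respectively". Checking sphericity with Mauchly's test points to the classical form of repeated measures ANOVA.

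Table 1 (Follow-up surveys) schedules the PHQ-9 and four other scales at T0, T1, T2, T3 and T4-6, which is seven assessments. The sample size paragraph in Methods says "a drop-out rate of 25% can be expected based on previous experience with longitudinal studies", and the Discussion concedes that "the follow-up assessments can also be a limitation if a lot of participants drop out of the study".

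The regression paragraph of the Statistical analysis section plans random-intercept generalized linear mixed models with two goals: determinants of onset, and prediction of occurrence and course. The same paragraph says that missing follow-up questionnaires will be handled by sensitivity analyses and, where suitable, by imputation. It does not say whether this extends to the tests listed earlier.

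**The concern.** Cochran's Q, Friedman's test and classical repeated measures ANOVA work on complete blocks. A patient who misses one of the visits under test is removed entirely, including the questionnaires that were returned. The paired t-test and the Wilcoxon signed-rank test lose every incomplete pair. The protocol names these tests for change over time and also expects a quarter of the cohort to leave.

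Two things are at stake. The first is precision: data already collected are thrown away, and the loss grows with the number of visits in the test. The second is representativeness: if depressed patients are more likely to stop answering, those left are on average less depressed than the cohort. A method that avoids the first problem and reduces the second is already within the plan's framework. As the text stands, it is not given the job of testing change over time.

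**Working it through.** **Inputs from the protocol article.** Recruitment target 500, number needed 380 and drop-out 25% (Methods, sample size paragraph); seven PHQ-9 assessments, six of them follow-ups (Table 1).

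**Step 1: the plan's own drop-out figure.** The protocol states "the sample size needs to be at least 380 to achieve a statistical power of at least 0.8". Inflating for drop-out gives 380 / (1 − 0.25) = 507, against a target of at least 500. That agrees within 3%. In the other direction, 500 × 0.75 = 375.

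**Step 2: patients left in a test over T0-T6 without imputation.** Let m be the chance that a patient who stays misses any one follow-up questionnaire, taken as independent across visits. The document gives no value for m, so a range is shown.

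Complete series = 500 × 0.75 × (1 − m)^6

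| m (assumed) | Complete series | Lost |
|---|---|---|
| 0% | 375 | 25% |
| 2% | 332 | 34% |
| 5% | 276 | 45% |
| 10% | 199 | 60% |

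The first row follows from the protocol's own drop-out rate. The other rows rest on the assumed m.

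**Step 3: what an all-available-records analysis keeps.** It uses every patient with at least one measurement, up to 500. It cannot supply T6 answers from patients who have left. At m = 5% it would have 375 × 0.95 = 356 observed values at T6, against 276 in a complete-block test, and more at earlier visits.

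**Step 4: possible bias, flat prevalence.** Simulation of 200,000 patients; true prevalence 20% at every visit; logistic random intercept with SD 2; total drop-out 25%. The odds of leaving before the next visit are multiplied by an assumed odds ratio (OR) when PHQ-9 status is positive.

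| OR (assumed) | Completers at T0 | Completers at T6 | Spurious change |
|---|---|---|---|
| 1.5 | 19.1% | 19.4% | 0.3 points |
| 2 | 18.3% | 18.7% | 0.4 points |
| 3 | 17.2% | 18.0% | 0.8 points |

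With no link between depression and drop-out, completers show 20.0%.

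**Step 5: possible bias, falling scores.** A second simulation uses a PHQ-9-like score (mean 7, falling 0.3 per visit, between-person SD 3.5, within-person SD 3, all assumed), again with 25% drop-out. The share at or above 10 falls as follows.

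| Drop-out odds per SD of score (assumed) | Full cohort T0 to T6 | Completers T0 to T6 | Understatement of the fall |
|---|---|---|---|
| about 1.3 | 25.9 − 15.0 = 10.9 | 24.4 − 14.0 = 10.4 | 0.5 points |
| about 1.6 | 25.7 − 14.9 = 10.8 | 22.5 − 12.8 = 9.7 | 1.1 points |
| about 2.1 | 25.9 − 14.9 = 11.0 | 21.3 − 12.0 = 9.3 | 1.7 points |

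**Step 6: bias against noise.** The standard error of a paired T0-T6 difference is √[2p(1 − p)(1 − ρ)/n]. With n = 375, p = 0.18 and an assumed within-person correlation ρ of 0.2 to 0.6:
- ρ = 0.2: √(2 × 0.18 × 0.82 × 0.8 / 375) = 2.5 points
- ρ = 0.6: √(2 × 0.18 × 0.82 × 0.4 / 375) = 1.8 points

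The bias in change lies below this range, and only the strongest scenario (1.7 points) comes near its lower end.

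**The case against.** The strongest reply is that the tests belong to the exploratory layer. They follow an opening sentence about descriptive and explorative analysis, while prediction of the course of depression is given to mixed models that accept incomplete series. This stands in part. A reader might infer that the study will assess the course of depression in completers only; the regression paragraph contradicts that. But the models' stated goals are determinants and prediction. Whether scores or prevalence change over time is assigned to the listed tests, with significance testing and post-hoc comparisons, and no precedence is stated should the two analyses disagree.

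Second, a reader might infer that every one of these tests loses at least 25%. The text does not support that. It does not say that each test spans T0-T6, and the list includes two-visit tests. A T0-T1 comparison keeps patients who leave later.

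Third, missing data are addressed, in general terms. The sentence is not worded as limited to the models, so a claim that the tests will certainly run without imputation goes too far. Equally, nothing links it to them, and it is conditional. The full analysis plan may settle this, but the named choice of complete-block tests stands in the article.

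Fourth, the harm from bias is easily overstated. It would be too strong to call the tests valid only when drop-out is unrelated to depression. Dependence on a patient's level of depression mainly moves the level of prevalence; within-person change is affected much less (Steps 4 to 6). That objection stands.

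**Conclusion.** The point holds as a correctable choice of method. It does not threaten the main models. The firm part is lost precision: any complete-block test over T0-T6 without imputation keeps at most 375 of 500 patients at the protocol's own drop-out rate. It keeps about 332 to 199 if stayers also miss an assumed 2% to 10% of single questionnaires.

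The conditional part is bias. If drop-out depends on depression, which the document does not quantify, completer prevalence is off by roughly 1 to 3 points in the flat-prevalence setting, for example about 18% against a true 20% at an odds ratio of 2. The bias in change is smaller: 0.3 to 0.8 points there, and 0.5 to 1.7 points under the falling-score assumptions.

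A reader might also infer, because 375 is below 380, that the time-trend tests are underpowered. The documents do not support that: 380 was derived for the effect of a determinant on depressive symptoms, not for change over time.

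**What to change.** State that inference on change over time comes from the planned mixed-model framework: visit (T0-T6) as a categorical fixed effect, all available records, and means or prevalences per visit with confidence intervals and contrasts against T0. For binary outcomes, average the per-visit prevalences over the random intercept, because a random-intercept logistic model does not give population prevalence directly. Keep Cochran's Q, Friedman's test, repeated measures ANOVA and the paired tests as a labelled completer sensitivity analysis, or state that they are run on imputed data.

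The cost is modest but not nil. The protocol does not yet specify visit as a categorical effect, and the averaging step adds some work. The result rests on a missing-at-random assumption, which the sensitivity analyses already foreseen for missing questionnaires could examine. No change to data collection is needed.
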